### Statistical analysis

Data will summarised and reported in adherence with CONSORT guidelines. The analysis of the primary outcome (IS) will use a generalised linear model (ANCOVA), with covariates for area at risk, diabetic status and centre. Only participants that have primary outcome data will be included in the analysis, no attempt will be made to impute data for participants that cannot, for whatever reason, contribute CMR data in the primary analysis. We will test the robustness of results to missing data by conducting sensitivity analyses to suit the pattern of missing data that arises. Secondary analyses will be conducted in a similar manner, using models suitable for the outcome. Blood sample outcomes will be analysed by first deriving an area under the curve and then using a similar strategy to the primary outcome. All estimates of effect will be presented with 95% confidence intervals. All analyses will be done in Stata (StataCorp. 2009. *Stata Statistical Software: Release 11*. College Station, TX: StataCorp LP.)

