There is extensive literature on successful pre, per and post conditioning interventions in animal models of AMI, which have resulted in reduction in final infarct size by up to 50%. Unfortunately, in spite of these very promising results in animal models, translation into benefit in human studies has been inconsistent. There may be several reasons for the poor translation into humans: (i) patients have multiple comorbidities that may make the heart more resistant to conditioning (e.g. age, hypertension and diabetes) [12,13]; (ii) prompt reperfusion with PPCI may minimise the potential benefit from conditioning strategies. Indeed, there is evidence from some of the human intervention studies that the benefit is largely confined to patients with larger infarcts, particularly those associated with occlusion of the left anterior descending artery [14]; (iii) it is known that spontaneous opening and closing of the occluded coronary artery (intermittency) is common in acute myocardial infarction [15], potentially replicating direct post conditioning and in this context any additional conditioning intervention may have limited therapeutic impact.

Nevertheless positive studies in humans have been reported. Remote (forearm) ischaemic perconditioning in acute ST elevation MI (STEMI) (administered in the ambulance *en route* to hospital for PPCI) resulted in a reduction in IRI – expressed as an increase in myocardial salvage compared to a placebo intervention. Although this did not translate into a significant reduction in infarct size for the whole group, a reduced infarct size was seen in the subgroup of patients with left anterior descending coronary artery occlusions [14]. Pharmacological postconditioning using cyclosporine administered prior to PPCI in acute STEMI was reported to decrease the area under the curve for the biomarkers creatine kinase (CK) and Troponin (the primary end point) and a reduction in infarct size (assessed by gadolinium late enhancement on cardiovascular magnetic resonance imaging (CMR) performed at five days) was reported in a subgroup of 27 patients [16].

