### Inclusion criteria

Men aged ≥18 years, women aged ≥55 years, and women <55 years who are sterilised, or have had a hysterectomy or have effective contraception and therefore with no possibility of being pregnant;

Presenting within 12 hours of the onset of chest pain and with ECG findings of ST segment elevation of more than 1mm in two contiguous limb leads or 2mm elevation in two contiguous chest leads or new left bundle branch block (LBBB) and for whom the clinical decision has been made to treat with primary PCI;

Patients with posterior infarcts with anterior ST segment depression who meet the other inclusion criteria can also be included;

Occlusion of the culprit related artery (TIMI grade 0 or TIMI grade 1);

Of North European descent.

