### Statistics

#### Proposed sample size

The primary outcome measure in this study will be the infarct size. We will estimate the difference in infarct size between the treatment and intervention group correcting for area at risk (AAR) and diabetic status using an analysis of covariance framework (ANCOVA) to take advantage of the correlation between IS and AAR to reduce sample size. Data from [name] (personal communication) and the Aarhus study [14] suggest that the AAR in this cohort would be approximately mean 30% (standard deviation 15), and that the IS in the placebo group should be between mean 15% (from Aarhus) to 20% (from [name]) (standard deviation 11). We have chosen the lower of these values because this estimate was from clinical trial data. Data from both these data sets indicate that correlation between AAR and IS is above 0.60. The estimate of treatment effect in the Aarhus study was a reduction of IS from 15% in the control to approximately 9% in the intervention group, a reduction of 6%. This trial proposes more conservative, but still clinically relevant treatment effect size of 4% between the treatment and control group (a standardised effect size of about 0.36).

To explore statistical power and estimate sample size for the trial we used Monte Carlo simulation in Stata 11. (StataCorp. 2009. *Stata Statistical Software: Release 11*. College Station, TX: StataCorp LP.) A model based the above assumptions was used to simulate 10,000 trial data sets for a variety of sample sizes. The simulated data sets were analysed using ANCOVA to reflect the primary trial analysis. The proportion of simulated trials that return p-values less than 0.05 was then counted to evaluate the power of ANCOVA. A sample size of 150 (75 per group) will provide 90% power to detect a difference of 4% between treatment and control group in IS corrected for AAR. The sample size has been expanded by approximately 30-35% to account for loss of outcome measure due to death, those who decline CMR or are unsuitable for CMR due to renal dysfunction and those in whom the CMR scans are technically inadequate. We therefore plan to recruit 200–210 participants.

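### The primary ANCOVA could also adjust for onset-to-injection time and culprit artery, both knowable before injection, for a modest gain in precision

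*Protocol article*

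**What the plan says.** The Statistical analysis section fixes the primary model: it "will use a generalised linear model (ANCOVA), with covariates for area at risk, diabetic status and centre". The Proposed sample size section describes the same ANCOVA with AAR and diabetes, and states "A sample size of 150 (75 per group) will provide 90% power to detect a difference of 4% between treatment and control group".

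The Inclusion criteria require "Presenting within 12 hours of the onset of chest pain" and also "Occlusion of the culprit related artery (TIMI grade 0 or TIMI grade 1"). The last Exclusion criterion names the LAD, LCx and RCA as the possible culprit vessels. The time of onset and the culprit artery are therefore known before the study drug is given.

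Two other sections bear on whether these variables matter:

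- The Background reports that in some earlier human studies "the benefit is largely confined to patients with larger infarcts, particularly those associated with occlusion of the left anterior descending artery".
- Analysis of images justifies the endocardial surface area (ESA) measure of AAR by describing infarction as starting beneath the endocardium and spreading outwards through the wall.

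**The concern.** Adjusting for baseline variables that predict the outcome narrows the confidence interval for the treatment effect, and treatment cannot affect such variables. This plan relies openly on covariate adjustment for its power, yet its one covariate with a stated correlation, AAR, is read from the scan at 6–8 days.

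The document's own wavefront rationale suggests that ESA captures the endocardial extent of the infarct and leaves its transmural depth in the residual. Time from onset is a natural predictor of depth, so it may carry information that AAR does not. Culprit artery is a second candidate, although part of its effect will already run through AAR. At stake is some precision in a trial with about 75 evaluable patients per arm.

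**Working it through.** **Inputs** (Proposed sample size): SD of infarct size 11; difference 4 points; 75 per group; correlation ρ between AAR and infarct size given only as above 0.60; significance threshold 0.05. Sidedness is not stated, so two-sided is assumed.

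**Formulas.** Residual SD = 11 × √(1 − ρ²). SE = residual SD × √(2/75). Power = Φ(4/SE − 1.96).

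**1. The plan's own 90%.**
- At ρ = 0.60: residual SD = 11 × 0.80 = 8.80; SE = 8.80 × 0.1633 = 1.437; 4/1.437 = 2.78; power 79.5%. A noncentral t calculation gives 79.0%, and 10,000 simulated ANCOVA trials give 79.0%.
- For 90% power, the residual SD must be 4/[0.1633 × (1.960 + 1.282)] = 7.56, so ρ = √(1 − (7.56/11)²) = 0.73.
- At ρ = 0.73: residual SD 7.52; SE 1.228; power 90.3% (simulation 89.5%).

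The stated 90% is compatible with a correlation above 0.60, but the figure 0.60 itself does not reproduce it. Both values serve as baselines below.

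**2. Effect of the extra covariates.** Let p be the share of residual variance that they explain after AAR, diabetes and centre. The residual SD is multiplied by √(1 − p). The document gives no value for p, so 5% and 10% are assumptions.

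| ρ | p | Residual SD | Power, 75 per group | 95% CI half-width |
|---|---|---|---|---|
| 0.60 | 0 | 8.80 | 79.5% | 2.82 |
| 0.60 | 0.05 | 8.58 | 81.5% | 2.75 |
| 0.60 | 0.10 | 8.35 | 83.5% | 2.67 |
| 0.73 | 0 | 7.52 | 90.3% | 2.41 |
| 0.73 | 0.05 | 7.33 | 91.7% | 2.35 |
| 0.73 | 0.10 | 7.13 | 93.0% | 2.28 |

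In patient numbers this is worth 1/(1 − p): 1/0.95 = 1.05 and 1/0.90 = 1.11, or about 5–11% more patients. The loss of degrees of freedom hardly shows. At ρ = 0.60 and p = 0, the noncentral t power is 79.0% with three fitted parameters and 78.9% with ten.

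**3. Could they restore 90% at ρ = 0.60?** They would need p = 1 − (7.56/8.80)² = 0.26, well above the range assumed here.

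**4. Culprit artery after AAR.** Let a be its correlation with AAR and c its correlation with infarct size. Its partial R-squared at ρ = 0.60 is (c − 0.60a)² / [0.64 × (1 − a²)]. With assumed a of 0.3 or 0.5 and c of 0.2 to 0.4, this runs from 0 to 0.08. The top value is (0.40 − 0.18)²/(0.64 × 0.91) = 0.083. The gain from culprit artery alone could be nil.

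**5. Which time to use.** Trial hypothesis and the dose section both place the injection before the artery is opened. Onset-to-reperfusion time therefore ends after treatment, whereas onset-to-injection time does not. The 12-hour limit applies to presentation, so it does not cap the duration of ischaemia.

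**6. Missing onset times.** If patients without an onset time were dropped, a fraction m lost would scale the variance by (1 − p)/(1 − m). The gain vanishes when m = p: 5% missing cancels a 5% gain.

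**The case against.** The strongest reply is that the document contains no error here. It prespecifies a short covariate list, and leaving out prognostic covariates does not bias a randomised comparison. That stands. Chance imbalance in delay or territory is already reflected in the standard error, and a condensed article cannot be faulted for stratification details that it does not give.

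A reader might infer more than the text supports in four ways.

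- **That the omitted variables are strong predictors.** No section quantifies their effect after AAR, and culprit artery may add almost nothing.
- **That the plan needs them to reach its power.** At a correlation of about 0.73 it reaches 90% without them; at 0.60 they would have to explain about 26% of residual variance. The unstated correlation in the simulation is a separate matter.
- **That TIMI 0 versus 1 also belongs in the model.** Eligibility already restricts it to two adjacent grades, and nothing in the text says that the distinction predicts infarct size.
- **That the Background remark on LAD occlusion calls for a treatment-by-LAD term.** Such a term adds no precision to the main effect, and effect-modifier analyses may sit in an analysis plan that is not shown. Power would also be low. With an assumed even split and residual SD 8.80, its SE is 8.80 × √(4/37.5) = 2.87, and power for a 4-point interaction is Φ(4/2.87 − 1.96), under 30%.

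It is also fair to say that eligibility criteria show what must be known, not what is recorded as data.

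**Conclusion.** The point holds as a modest suggestion on efficiency. The model omits two plausible prognostic variables that are established before injection. Adding them may raise power by about 2–4 points if the correlation is 0.60, or by about 1–3 points if it is 0.73. These figures rest on an assumed further 5–10% of residual variance explained, two-sided testing at 5%, SD 11 and 75 evaluable patients per arm. The case is better for time from onset than for culprit artery. The treatment estimate is not biased without them, and the stated 90% power is neither refuted nor rescued by this point.

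**What to change.** Before unblinding, extend the primary ANCOVA to: treatment, AAR, diabetes, centre, symptom-onset-to-injection time (continuous, with its functional form stated) and culprit artery (LAD versus non-LAD).

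First confirm that onset time, injection time and culprit vessel are captured on the trial forms. The blood-sampling schedule runs from injection, which suggests that injection time is noted, but the article does not say so. State a rule for missing onset times that keeps those patients in the analysis, such as simple imputation of the baseline value made without regard to arm.

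The cost is two degrees of freedom, a change of wording in the analysis section and the missing-value rule. If either variable proves not to have been captured, leave it out; the existing model remains valid.

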### Trial oversight committees

#### Data Monitoring Committee (DMC)

The DMC includes three independent members, including an independent statistician. The committee will meet regularly to monitor the unblinded trial data and serious adverse events and make recommendations as to any modifications that are required to be made to the protocol or the termination of all or part of the trial.

### Trial Steering Committee (TSC)

The TSC includes three independent members. The committee will meet regularly to provide oversight for the trial.

### Ethics and regulatory approvals

This protocol and related documents have been reviewed by Scotland A Research Ethics Committee. The study has also received clinical trial authorisation from the Medicines and Healthcare products Regulatory Agency (MHRA) (EudraCT number: 2010-023571-26). Appropriate approvals are in place for the Australian site. The study conforms with the principles of the Declaration of Helsinki and the European Clinical Trials Directive.

### Strengths and weaknesses of this study

This is the first multi-centre, randomised, placebo-controlled and double-blinded trial of sodium nitrite as a conditioning agent in man. We use a robust method of accurately delineating infarct size and area at risk using CMR imaging techniques alongside the standard use of biomarkers. Due to the risk of methaemoglobinaemia in patients at risk of G6PD deficiency, only those of Northern European descent will be recruited. Further studies need to be conducted in other ethnic groups.

## Conclusion

Whilst huge strides have been made to reduce myocardial infarct size by timely opening of the infarct related artery, firstly ischemia and subsequently reperfusion itself cause substantial myocardial injury. Effective therapy to reduce this injury is urgently required if we are to make further progress in limiting infarct size, thereby reducing the subsequent development of heart failure. Whilst soundly based on animal studies, this proposal would be the first in man study to investigate whether intravenous infusion of sodium nitrite reduces myocardial infarct size.
